## Abstract

**Background:** Type 2 Diabetes mellitus (T2DM) is a major risk factor for cardiovascular diseases and increase mortality. Clinical outcomes of patients after percutaneous coronary intervention (PCI) were worse in T2DM patients than those without T2DM. New-onset diabetes after PCI (NODAP) is often observed during long-term follow-up and this further aggravates cardiovascular diseases. Several studies had focused on patients after PCI with known T2DM. Previous studies showed that impaired glucose tolerance and aging are risk factors that promote NODAP. Considering the unique characteristics of patients after PCI, we will further study relevant risk factors. We sought to investigate the potential predictors of acute coronary syndrome patients with NODAP by a multicenter retrospective cohort study.

**Methods:** This is a multicenter retrospective cohort study including patients after PCI. Clinical medical records of these patients were collected from four hospitals in different areas in China, from 2010 to 2021. Patients' demographic information, medical history, diagnostic testing, PCI-related information, medication situation will be summarized using descriptive statistics, and correlation analysis was performed on the development of new-onset diabetes. Variation will be described and evaluated using χ^2^ test or Kreskas-Wallis test. The prediction model will be verified by a validation set.

**Discussion:** A novel diabetes prediction model for patients after PCI is established, and this study can achieve advanced intervention for the occurrence of NODAP. Owing to its retrospective nature, this study has some limitations, but it will be further studied through supplement data collection or prospective study. The study has been registered for clinical trials by the Chinese Clinical Trial Registry (**ChiCTR2100047241**).

## Introduction

Type 2 Diabetes mellitus (T2DM) is a major health concern worldwide, with a prevalence of about 463 million by 2019, and a 62% increase since 2009 (1). In Chinese adults, the estimated T2DM and pre-T2DM prevalence are 10.9% and 35.7% (2), respectively. It is a strong risk factor for cardiovascular artery disease (CAD) and major adverse cardiovascular events (MACE) (3–5). A pooled analysis involving more than 1 million participants in Asia found that patients with T2DM had a higher risk (hazard ratio, 1.89) of all-cause death than those without T2DM (6). People are conferred an eight fold increase in death risk by unrecognized myocardial infarction (MI) with diabetes (7). As patients with acute ST-segment elevation myocardial infarction (STEMI) significantly improved after percutaneous coronary intervention (PCI), the 10-year survival rate was nearly 76% (8). Prolonged life expectancy makes chronic care management after PCI a concern. Nearly half of the inpatients with MI complicated with T2DM (9, 10) and good blood glucose control is one of the keys. There have been multiple studies regarding clinical outcomes in patients after PCI with known T2DM (11, 12). Patients after PCI with chronic T2DM emerge with poor clinical outcomes and different treatment strategies (13, 14). Patients approximately 30% who underwent PCI suffer from diabetes (13). Considering the counter-balancing effects of hemorrhagic and ischemic complications, the recent ultra-short DAPT strategy may not be suitable for patients with T2DM (15). New-onset of diabetes after PCI (NODAP) has attracted much attention; a 5-year survival of patients after revascularization with diabetes were worse (16). Among 3,683 acute coronary syndrome (ACS) patients (without T2DM before PCI), 436 patients (11.8%) developed NODAP after a follow-up of 3.41 ± .9 years (10).

However, the risk factors and pathophysiological mechanisms for NODAP remain unknown. The risk factors for NODAP may be different from those for simple diabetes. Patients after PCI are generally elderly, and are associated with a variety of metabolic diseases (obesity, hyperlipidemia, etc.) and stress states related to surgery; all the above predict the risk of T2DM. Previous studies show that abnormal heart rate variability is a risk factor for diabetes (17), and heart rate variability (low SDNN) is common in patients undergoing PCI (18). High intensity statins (19, 20) also has adverse effects on diabetes.

We propose leveraging advancements in machine learning by systematically comparing different modeling approaches (21), to develop a prognostic tool for NODAP. Therefore, we put forward the following hypothesis:

Refer to common risk factors such as obesity and smoking and explore the risk factors for NODAP; probing the risk of NODAP in different types of ACS patients (STEMI, NSTEMI, and UA) is equal or not.Systematically apply several machine learning algorithms to establish a predictive model of NODAP and verify its effectiveness.In this study, we sought to investigate the potential predictors of ACS patients with NODAP and comparatively evaluate performances of these predictive models with each other, to identify which is the most accurate.

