**Patient information**	
Demographic information	age, sex, ethnicity (nationality/ethnic minorities), marital status, Occupation (physical and non-physical)
Medical history	the type of ACS (STEMI, NSTEMI, UA), smoking history, alcohol consumption history, history of hypertension, history of hyperlipidemia, history of chronic diseases, family history of T2DM, family history of CAD
Diagnostic testing	height, weight, body mass index (BMI), blood pressure, resting heart rate, fasting blood glucose, HbA1c, serum uric acid level, triglyceride level, total cholesterol level, low density lipoprotein level, left ventricular ejection fraction (LVEF)
PCI surgery-related information	number of diseased vessels, number of stent implantation, total length of the stent
Medication situation	statin medications (low intensity, high intensity), traditional Chinese medicine (Yes or No)

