### Statistical Analysis

Baseline demographic characteristics and study outcomes conforming to normal distribution were expressed as mean ± standard deviation. The *t*-test was used for comparison between the two groups. The measurement data not conforming to normal distribution was represented as the median (quaternary interval), and the comparison between the two groups was performed using the Mann–Whitney *U* test. Descriptive statistics will be used for the overall cohort and aggregated statistics will be calculated. Descriptive statistics are used for the entire queue and the aggregated statistics are calculated. Enumeration data were expressed as frequency or percentage, and χ*2* test was used for comparison between the two groups. Univariate analysis was conducted for all factors first, and statistical learning methods such as tree integration algorithm and Lasso regression were adopted to compare and screen related risk factors from multi-dimensional perspectives. To avoid omission of important variables, covariates with *P* < 0.01 in univariate analysis and important factors screened by statistical learning method were included in multivariate logistic regression analysis. Independent risk factors for NODAP were analyzed by progressive forward regression analysis, and the OR value of each related factor and its 95%CI were estimated. *P* < 0.05 on both sides of all tests indicated statistically significant differences.

We will evaluate the potential predictors of NODAP informed by prior literature (10, 20). The data set will be randomly divided into a training dataset and an internal validation dataset in a 5:5 ratio. We will include all a priori selected variables in the final model; the Bootstrap method was used for model internal validation in this data set. If necessary, non-normally distributed variables will be transformed using the Box-Cox transformation. The validation will be established with the same inclusion and exclusion criteria and sensitivity analyses will be performed. All analyses were performed using R3.6.1 and SPSS^®^ Statistics 21 software (IBM^®^, Armonk, NY, USA). Prism 5 (GraphPad Software Inc., San Diego, CA, USA) is used for drawing statistical graphs.

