### Sample Size

Based on prior studies and conditions of each hospital (31), the number of PCI surgical interventions is between 10,000 and 15,000 in the past 10 years and in which 6.1–11.6% patients (10, 32) may develop NODAP (at least 610 patients). For the exploratory analysis of multiple risk factors, ≥10 events per variable (EPV) are necessary to obtain sufficient degrees of freedom, with the assumption of at least 20 patients with the outcome (NODAP) per predictor variable (33). The ratio of the two groups is set to 5:5 (validation dataset: training dataset); the sample size could be calculated as 300 in both the training set and an internal validation set. The actual sample size may be larger than the calculated amount, thus it will be adjusted according to the situation.

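### The protocol asks whether NODAP risk is equal across STEMI, NSTEMI and UA, but its selection-based analysis can drop ACS type without an interval estimate, and a non-significant result cannot support 'equal'

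*Protocol article*

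**What the plan says.** The Introduction of the protocol article lists, under its hypotheses, a search for risk factors for NODAP together with "probing the risk of NODAP in different types of ACS patients (STEMI, NSTEMI, and UA) is equal or not". Table 2 carries ACS type as one candidate predictor, a three-level factor: "the type of ACS (STEMI, NSTEMI, UA), smoking history".

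The route to an answer is in Statistical Analysis:

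- Covariates with P < 0.01 "in univariate analysis and important factors screened by statistical learning method were included in multivariate logistic regression analysis".
- After that, "Independent risk factors for NODAP were analyzed by progressive forward regression analysis", and "the OR value of each related factor and its 95%CI were estimated".
- The general significance rule is that P < 0.05 "on both sides of all tests indicated statistically significant differences".
- A separate sentence says "We will include all a priori selected variables in the final model", but the article does not name those variables.

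Sample Size works from events per variable and concludes that "the sample size could be calculated as 300 in both the training set and an internal validation set". It gives no effect size or precision target for the ACS-type comparison. Limitations describes the analyses as exploratory.

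**The concern.** A question of the form 'equal or not' has two possible answers. The stated rule supports only one of them: a small P value supports 'not equal'. Nothing says what evidence would support 'equal', or that a null result may simply be inconclusive.

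The selection steps add to this. ACS type has to survive a screen and then forward selection before an adjusted odds ratio and interval are called for, unless it is one of the unnamed a priori variables. If it is dropped, the report could say that ACS type was not an independent risk factor and give no interval to show how large a difference remains possible. A reader who recalls the hypothesis would be tempted to take this as evidence of equal risk.

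**Working it through.** **Figures in the plan.** Sample Size gives 10,000-15,000 PCI procedures and a NODAP rate of 6.1-11.6%. Its minimum of 610 events reproduces: 10,000 × 0.061 = 610. Half is 305, close to the stated 300. The 30 variables that I count in Table 2, at 10 events each, also give 300. So 300 fits best as events per set, although the text does not say whether it means events or patients. No power is stated for ACS type, so there is no power figure to reproduce.

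**Assumptions.** The STEMI/NSTEMI/UA split is not in the document. I used four: equal thirds, 30/20/50, 25/10/65 and 15/15/70. NSTEMI has odds raised by OR 1.25 or 1.5 against the other two types, and the baseline odds are solved so that total events match the plan. All 10,000 procedures are treated as eligible patients. That is generous, because the eligibility criteria will remove some.

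**Formula.** For the 2-df chi-square test the noncentrality is

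λ = N × Σ wᵢ(pᵢ − p̄)² / [p̄(1 − p̄)],

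and the chance of missing the difference is P(χ²₂(λ) < 5.991) at the 0.05 level.

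**Worked case:** N = 10,000, 610 events, equal thirds, OR 1.25. The solved risks are 0.05661 (STEMI, UA) and 0.06978 (NSTEMI), with p̄ = 0.061.

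λ = 10,000 × [⅔ × (0.05661 − 0.061)² + ⅓ × (0.06978 − 0.061)²] / (0.061 × 0.939) ≈ 6.7, so the miss probability is 0.36.

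**Range over the four mixes, 6.1% rate:**

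| Data used | Level | OR 1.25 missed | OR 1.5 missed |
|---|---|---|---|
| 10,000 patients, 610 events | 0.05 | 36-68% | 1-14% |
| 10,000 patients, 610 events | 0.01 (univariate screen) | 60-86% | 3-32% |
| 5,000 patients, 305 events | 0.05 | 64-82% | 13-45% |
| 5,000 patients, 305 events | 0.01 (univariate screen) | 84-94% | 30-68% |

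If 300 meant patients per set (18-35 events at 6.1-11.6%), OR 1.5 would be missed in 85-92% of cases at 0.05.

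The 0.01 rows show how often ACS type would fail the univariate screen. They are not the chance that it is lost altogether, because the learning-based screen or the a priori list could still bring it in.

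**What an interval would show.** For NSTEMI against UA with an observed OR of 1, SE = √{[1/w(NSTEMI) + 1/w(UA)] / [N p̄(1 − p̄)]}.

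- Full cohort, equal thirds: √(6 / 572.8) = 0.102, 95% CI 0.82-1.22.
- Full cohort, 25/10/65: √(11.54 / 572.8) = 0.142, 95% CI 0.76-1.32.
- Training half: 0.75-1.33 (equal thirds) to 0.67-1.48 (25/10/65).

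**Could equality be claimed?** Take two one-sided tests at 0.05, a margin of 0.80-1.25 (assumed) and a true OR of 1. For 80% power the number needed per ACS type is 2(1.645 + 1.282)² / [0.061 × 0.939 × (ln 1.25)²] ≈ 6,006. Equal thirds of 10,000 give about 3,333. Power for the NSTEMI-UA comparison is then 2Φ(0.2231/0.1023 − 1.645) − 1 ≈ 0.41. Under 25/10/65 the 90% CI at an observed OR of 1 is about 0.79-1.26, so it cannot fit inside the margin.

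**The case against.** The strongest reply is that this is an ordinary test of difference within an exploratory risk-factor search. ACS type is one of about 30 candidates, the clause is half of one hypothesis item, and such a search needs no equivalence margin. That stands, and it lowers the severity.

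Three stronger readings are tempting, and the document does not support them:

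- *That a non-significant test will be reported as equal risk.* Statistical Analysis defines only what a significant result means. It is silent on a non-significant one.
- *That P < 0.05 is the only rule.* There is also the P < 0.01 screen, tree-based and Lasso screening, forward regression, and odds ratios with 95% CIs for the factors found to be related.
- *That the lack of a margin is itself an error.* A margin matters only if equality is to be claimed.

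It is also fair to say that ACS type, being named in a hypothesis, may be among the a priori variables that go into the final model, in which case much of the problem disappears. The article does not say so. Frequencies by outcome group would let a reader work out crude odds ratios, but no interval for them is planned.

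On size, the ACS mix is assumed and the effect is placed on NSTEMI, which is never the largest group in the mixes used. With the full cohort OR 1.5 is seldom missed. The high miss rates there concern OR 1.25, and the document does not say whether that difference matters clinically. None of this makes a null result evidence of equality, and none of it guarantees that an interval is reported.

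**Conclusion.** The point holds as a mismatch between the question and the route to its answer. The hypothesis allows 'equal' as an answer, while the analysis works by significance and selection and secures an interval only for factors that count as related. A null result on ACS type could therefore appear without the one quantity that would show how informative it is.

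How much this matters depends on which data are used, and the article does not say whether the logistic model is fitted in the training half or the whole cohort. In the full cohort a null result would usually rule out a difference as large as OR 1.5 but not OR 1.25. In the training half it would often rule out neither. These statements rest on the assumed ACS mixes, the 6.1% rate and the effect in NSTEMI; a rate nearer 11.6% would lower the miss rates.

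The misreading is a risk that the framing creates, not something the protocol commits to. Severity: minor.

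**What to change.** In the Introduction, state the aim as estimating differences in NODAP risk between ACS types. In Statistical Analysis:

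1. Name ACS type among the a priori variables and keep it in the multivariable model whatever its P value.
2. Report the STEMI-UA, NSTEMI-UA and STEMI-NSTEMI odds ratios with 95% CIs from the full cohort. The 5:5 split serves the prediction model, and this comparison does not need it.
3. State that P ≥ 0.05 will not be reported as equal risk.

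Add an equivalence margin only if the investigators wish to claim equality. It should then be set in advance and justified clinically; 0.80-1.25 would be largely out of reach at the planned size.

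The cost is a few sentences, one factor (two parameters) forced into a model that is already planned, and the possibility that the answer on ACS type has to be reported as inconclusive.

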## Methods and Analysis

### For Study Design

The study design and report are according to the methods section of the Strengthening the Reporting of Observational Studies in Epidemiology (STROBE) (22) for cohort studies. The retrospective study used hospital health records and third party databases as the data source and management platform. It is based on the program “evidence-based study of integrated Chinese and Western medicine in metabolic diseases of glycolipids” hosted by the China Academy of Chinese Medical Sciences (project number: 2020YJSZX-4) to develop the risk factors of NODAP. This multicenter, retrospective, cohort study will be carried out between June 2021 and December 2023 in four top hospitals from different districts of China. The recruitment and research sites are 1. Xian Hospital, China Academy of Chinese Medical Sciences, Beijing. 2. Beijing Anshan Hospital, Capital Medical University, Beijing. 3. The First Affiliated Hospital of Guangdong Pharmaceutical University, Guangdong. 4. Affiliated Hospital of Traditional Chinese Medicine of Southwest Medical University, Sichuan. Additional hospital sites may be added based on feasibility and resources available. The study has been registered for clinical trials by the Chinese Clinical Trial Registry (**ChiCTR2100047241**), which provided an overview of our methodology. Through the establishment of validation dataset and training dataset, machine learning is conducted and the prediction model is finally formed. The specific overview of our methodology is shown in Figure 1.

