### Data

The data extracted from the hospital information system (HIS) will exclude the privacy of participants; detailed parameters will vary based on each institution, which may include outpatient and inpatient medical history and diagnostic imaging database. To ensure the unified management of mass data among multiple institutions, we have established a third-party data management platform (*http://121.30.232.162:10094/#/user/login?redirect=%2F*). Every participant will be assigned a systemic number separate from the medical record number. Based on the platform, the required information can be retrieved and excluded. After machine retrieval by a third-party platform, two researchers will review each participant for inclusion in the study.

Using data provided from decision support at four hospital sites, we expect at least eligible patients in the period 2010–2021, and data according to the fields included in the diagnosis (acute coronary syndrome, PCI, diabetes, etc.) and CCCDNCE 2.0 codes. A standardized case report form (CRF) that has been pilot tested and refined will be used for data extraction. Trained researchers will enter the identified data directly using the electronic CRF into the online platform managed in Beijing, China.

Data will be collected with traditional Chinese and western medicine characteristics that are important in the management of ACS patients with NODAP to confirm the baseline level and severity of blood stasis syndrome. Data will be included in two stages. First, ACS patients who were eligible for inclusion criteria were included. All these patients will be re-screened to ensure the duration of 12 months of follow-up and above. Structural data such as demographic information, diagnostic testing and medication situation can be directly collected in the database. Medical history and surgery records will be retained in the platform in unstructured text format. Researchers in charge of each institution will ensure consistency on extraction method and content, and train individuals for data identification and extraction, and entering DE identified data using the electronic CRF. Relevant medical history including history of ACS, history of T2DM, history of PCI surgery will be collected to confirm the diagnosis. New-onset diabetes was diagnosed by fasting blood glucose or HbA_1_c levels in the outpatient or inpatient biochemical test during follow-up.

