### Potential Risk Factors

As the study is primarily retrospective, multiple initial information data will be collected and outcome data will be divided into one dimension: new-onset diabetes. Initial information data for five broad categories include (I) demographic information; (ii) medical history; (iii) diagnostic testing; (iv) PCI surgery-related information; and (v) medication situation. Detailed information refer to previous studies on risk factors for diabetes (27, 28) (Table 2). Variables with missing data other than demographic information (age, sex, ethnicity, marital status) will be dealt with using multiple imputation (29).

**Table 2 T2:** Patient information to be extracted.

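### No hospital term is named in the candidate list or in any risk-factor model step, so differences between the four pooled hospitals can appear as independent risk factors

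*Protocol article*

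**What the plan says.** All references are to the Protocol article.

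- **Sites (For Study Design).** Patients come from "four top hospitals from different districts of China": two in Beijing, one in Guangdong and one in Sichuan. One is a Chinese-medicine hospital by name ("Affiliated Hospital of Traditional Chinese Medicine of Southwest Medical University, Sichuan"), and another belongs to the China Academy of Chinese Medical Sciences. The list is open: "Additional hospital sites may be added based on feasibility and resources available".
- **Candidates (Potential Risk Factors, Table 2).** There are five categories with 30 items, among them statin intensity and Chinese medicine as a yes/no item. Hospital is not listed. Missing values outside a few demographic items "will be dealt with using multiple imputation".
- **Data content and outcome (Data).** For the hospital systems, "detailed parameters will vary based on each institution". On the outcome: "New-onset diabetes was diagnosed by fasting blood glucose or HbA_1_c levels in the outpatient or inpatient biochemical test during follow-up". No common testing schedule is stated.
- **Models (Statistical Analysis).** Covariates with univariate P < 0.01 and "important factors screened by statistical learning method were included in multivariate logistic regression analysis". Forward selection follows, and the retained terms are reported as independent risk factors with odds ratios and 95% confidence intervals. The 5:5 split into training and validation sets is random over the pooled data.

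**The concern.** Exploring risk factors is one of the two stated aims, so the odds ratios are a main product of the study. Some candidates are prescribing choices that may well differ between these hospitals, notably Chinese medicine and statin intensity. The recorded outcome depends partly on how often each hospital tests glucose or HbA1c, and testing frequency is not in Table 2, so no listed covariate can adjust for it. If hospitals that use more Chinese medicine also record more (or less) NODAP for other reasons, a pooled model attributes that difference to Chinese medicine.

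The random split does not guard against this. Both halves have the same hospital mix in expectation, so a spurious association found in one half will tend to recur in the other. The study sits within a programme on integrated Chinese and Western medicine, so a false harmful or protective odds ratio for Chinese medicine would bear directly on its subject.

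**Working it through.** **1. The plan's own figures (Sample Size).** 10,000 procedures × 6.1% = 610 events, as stated. Half is 610 / 2 = 305, against the stated 300 per set. These agree if 300 counts NODAP events. If it counted patients, a set would hold only 300 × 6.1% = 18 to 300 × 11.6% = 35 events. I use 305 training events below.

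**2. Crude pooled odds ratio when the true odds ratio is 1.0.** Take two equal hospital groups with NODAP rates r1 = 11.6% and r2 = 6.1%, and Chinese-medicine use u in the first group and 1 − u in the second. With no effect within either group:

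- rate in users = u·r1 + (1 − u)·r2
- rate in non-users = (1 − u)·r1 + u·r2

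| Use (assumed) | Users | Non-users | Pooled OR | OR if rates are reversed |
|---|---|---|---|---|
| 80/20 | 0.8×0.116 + 0.2×0.061 = 0.105 | 0.2×0.116 + 0.8×0.061 = 0.072 | (0.105/0.895)/(0.072/0.928) = 1.51 | 0.66 |
| 70/30 | 0.0995 | 0.0775 | (0.0995/0.9005)/(0.0775/0.9225) = 1.32 | 0.76 |
| 60/40 | 0.094 | 0.083 | (0.094/0.906)/(0.083/0.917) = 1.15 | 0.87 |

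The usage shares are assumptions. So is the allocation of the two rates to hospital groups: Sample Size gives 6.1–11.6% as an overall expected range from cited studies, not as a difference between hospitals.

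**3. Dependence on the assumptions.** This uses four equal hospitals in two pairs, a true odds ratio of 1.0, a training half of 5,000 patients and a two-sided 0.05 Wald test. Pooled results come from expected cell counts. All scenarios except the two under *Use or rate equal everywhere* were also simulated 1,000 times each, with and without three hospital indicators.

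| Scenario (use; NODAP rate) | Pooled OR | False positives, pooled | False positives with hospital indicators |
|---|---|---|---|
| 60/40; 9.5% vs 8.2% | 1.03 | about 6% | about 5% |
| 70/30; 10.0% vs 7.7% | 1.12 | about 21% | about 5% |
| 80/30; 11.6% vs 6.1% | 1.42 | about 93% | about 4% |
| 80/30; rates reversed | 0.71 | 92–93% | about 6% |
| Use and rate both vary, uncorrelated across hospitals | 1.00 | 5–7% | about 6% |
| Use or rate equal everywhere | 1.00 | 5% | not simulated |

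With hospital indicators the simulated odds ratio was 1.00–1.01 in every scenario. The false-positive rates depend on the number of events. At 11.6% and 6.1%, a half of 5,000 holds 5,000 × 8.85% = about 442 events, more than 305. With fewer events the false-positive rates would be lower, but the bias in the odds ratio would not change.

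**4. Cost in events per variable.** Counting each Table 2 item as one term gives 5 + 8 + 12 + 3 + 2 = 30. Then 305 / 30 = 10.2, and with three hospital indicators 305 / 33 = 9.2. The plan's stated minimum is 10. At its assumed 20 events per predictor, 305 / 20 supports about 15 terms, leaving about 12 after hospital.

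**The case against.** The strongest reply is that this argues from silence. The article condenses a fuller plan, Figure 1 and any separate analysis plan were not available here, and sensitivity analyses are mentioned without detail. Hospital is an attribute of the record rather than patient information, so its absence from Table 2 need not mean absence from the models. That limits the claim to: no hospital term is named. It does not remove the point, because the article itself fixes the candidate list, entry threshold, selection method and label for the results.

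Several other objections stand:

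- A reader might infer that hospital differences will be reported as risk factors. The documents do not support that. Bias requires exposure and recorded NODAP rate to be correlated across hospitals, and no hospital-level figures are given.
- Measured case mix (age, ACS type, BMI, fasting glucose, diseased vessels) and statin intensity are candidates themselves, so those differences are partly adjusted if selected. The odds ratios in step 2 are crude, not multivariable.
- A reader might infer that a variable one hospital never records will be filled in from the others. The article says content varies by institution, but it also specifies a standardized, pilot-tested case report form and site leads responsible for consistent extraction. It is not established that any hospital lacks a Table 2 variable.
- A reader might infer that the confidence intervals are too narrow because clustering is ignored. Nothing here establishes that. With use and rate uncorrelated across hospitals, the pooled test stayed close to its nominal level.
- A hospital indicator does not correct differences in testing between patients within one hospital.

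Limitations calls the analyses exploratory and associational and concedes possible selection bias. It does not mention hospital differences, and that caution sits poorly with calling the retained terms independent.

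**Conclusion.** The point holds as a conditional one. The stated route names no hospital term at any step, and the random split cannot reveal the consequence. If exposure and recorded NODAP rate are correlated across hospitals, hospital differences can appear as independent risk factors. Under the assumed shares and rates the crude odds ratio moves from 1.0 to between 1.15 and 1.51, or to between 0.87 and 0.66 in the other direction. With hospital differences as small as 60/40 use and 9.5% vs 8.2% NODAP it is 1.03, and with none or uncorrelated ones it is 1.00. These figures illustrate a mechanism and do not predict this cohort's result. The change should be made because it is cheap and removes between-hospital confounding from the reported odds ratios. The omission does not invalidate the study.

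**What to change.** In Statistical Analysis:

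1. Force hospital into the multivariable risk-factor model as a fixed factor not subject to selection. If sites are added, stratify by hospital or use a random intercept instead.
2. Report the odds ratios with and without hospital, so that readers can see which factors depend on it.
3. Include hospital in the multiple-imputation model.
4. If a hospital turns out not to record a variable at all, analyse that variable only in the hospitals that record it.

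The cost is a few sentences of wording and 3 degrees of freedom with four sites, more if sites are added as fixed terms. Events per variable fall from about 10.2 to 9.2 at 30 candidate terms and 305 training events. Staying at 10 or above allows 30 terms in total (305 / 10 = 30.5), so about three candidates would have to be dropped. If Chinese-medicine use is nearly determined by hospital, its adjusted odds ratio will be imprecise, which is a fair reflection of what the data can show. No new data collection should be needed, since the sites are named and the source hospital should be known for each record.
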